## Abstract

**Background:**

Several studies have shown that people with diabetes are at higher risk of experiencing a severe course of COVID-19 infection. However, it remains unclear whether diabetes per se is a risk factor for the development of Long/Post-COVID. In addition, there is a lack of nationwide, population-based studies on the epidemiology of Long/Post-COVID in people with diabetes. The aim of this project is to analyze: (1) incidence and time trends of Long/Post-COVID in people with and without diabetes between 2021 and 2023 in Germany as well as potential risk factors; (2) mortality, any hospitalization and hospitalization due to acute myocardial infarction, stroke, amputation and diabetic foot syndrome (DFS) after a Long/Post-COVID diagnosis, including an analysis of potential risk factors.

**Methods:**

This study is planned as a non-interventional longitudinal observational study based on statutory health insurance (SHI) data in Germany. The data holder is the Health Data Lab (HDL: data pool of billing data for all persons with statutory health insurance). The incidence rates of Long/Post-COVID will be estimated separately in the populations with and without diabetes and compared as corresponding relative risk. Moreover, we will analyse age- and sex-standardized mortality and hospitalization rates within 12, 24, and 36 months after a Long/Post-COVID diagnosis in the years 2021 to 2024. Potential uncertainties in diagnosing Long/Post-COVID (e.g., underreporting) will be addressed in sensitivity analyses.

**Discussion:**

The expected results will have high potential for use in epidemiological research on Long/Post-COVID, including the identification of potential risk factors in people with diabetes. The findings will serve to provide optimized healthcare for Long/Post-COVID patients with diabetes.

*Trial registration* The study has been registered in the German Clinical Trials Register with identifier DRKS00036279. Registration Date 15.05.2025.

**Graphical abstract:**

[figure not shown]

### Comorbidities / risk factors

Several studies described the association between certain comorbidities and the development of Long/Post-COVID (e.g. systematic review by Tsampasian et al. 2023 [11]):

Conditions associated with an increased risk of Long/Post-COVID include:Coronary heart disease (CHD): A meta-analysis of five studies with 201,906 patients reported a significantly increased risk of Long/Post-COVID among patients with pre-existing CHD (OR 1.28; 95% CI 1.19–1.38).Chronic obstructive pulmonary disease (COPD): A meta-analysis of 10 studies including a total of 257,340 patients found that COPD was a risk factor associated with the development of Long/Post-COVID (OR 1.38; 95% CI 1.08–1.78).Bronchial asthma: A meta-analysis of 13 studies involving 639,397 patients showed that patients with asthma had a significantly higher risk of developing Long/Post-COVID (OR 1.24; 95% CI 1.15–1.35).Anxiety and/or depression: A pooled analysis of four studies including a total of 634,734 patients found that the risk of Long/Post-COVID was significantly increased in patients suffering from anxiety or depression (OR 1.19; 95% CI 1.02–1.40).

Other diseases (e.g. chronic kidney disease, malignancies, and autoimmune disorders) encompass broad and clinically heterogeneous conditions that are difficult to capture with sufficient specificity using ICD codes in routine data.

### Role of diabetes

Diabetes mellitus is a widespread chronic disease with a global prevalence of 11.1% among adults aged 20 to 79 [12]. Diabetes mellitus is regarded as a risk factor for severe COVID-19, as indicated by increased rates of hospitalization, intensive care admission, and mortality [13]. However, it is not yet clear whether having diabetes per se is also a risk factor for developing Long/Post-COVID. A systematic review on this topic found that 44% of the studies identified diabetes as a risk factor for Long/Post-COVID, although the strength of this association varied considerably between studies [14]. This was partly due to the quality or design of the studies, e.g., a different definition of Long/Post-COVID, study population and study size, and the length of the observation period. In addition, no studies in Germany have yet compared the incidence of Long/Post-COVID in people with diabetes to people without diabetes.

People with diabetes exhibit chronic hyperglycemia, immune dysregulation, endothelial dysfunction, and a pro-inflammatory and prothrombotic state, which may exacerbate acute infection and promote persistent post-viral pathologies. In line with these mechanisms, studies suggest that diabetes mellitus may contribute to adverse long-term outcomes following SARS-CoV-2 infection including cardiovascular conditions [15, 16]. However, the association between diabetes and Long/Post-COVID, as well as its potential cardiovascular sequelae, remains incompletely understood.

Aims of this study are: 1) to estimate the incidence and time trends of Long/Post-COVID in people with diabetes compared to those without diabetes and to analyze potential risk factors for Long/Post-COVID; 2) to analyze mortality, any hospitalization, and hospitalization due to acute myocardial infarction, stroke, amputation, and DFS within 12, 24, and 36 months after Long/Post-COVID diagnosis in people with diabetes compared to those without, and to identify potential risk factors for these conditions.

## Methods/design

### Study design and data sources

This study is planned as a non-interventional longitudinal observational study based on secondary data from the SHI in Germany. The data holder is the Health Data Lab which hosts SHI data and facilitates their analysis through secure remote processing.

The SHI data contains comprehensive information on inpatient and outpatient care with exact dates, diagnoses, prescriptions, and some sociodemographic factors (age, gender, place of residence (urban/rural)). The diabetes status of insured persons is defined according to an established algorithm based on antihyperglycemic prescriptions and outpatient and inpatient diagnoses [17]. A diagnosis of Long/Post-COVID is considered as first or incident event per se (no counting of reinfections), as this diagnosis has only been established since 2021. In light of the clinically heterogeneous presentation of Long/Post-COVID and the documented supposed inconsistencies in ICD-10 coding practices across healthcare settings, we define Long/Post-COVID on the basis of the following diagnostic coding: U08.9 (Personal history of COVID-19, unspecified; this code is used if a previous confirmed COVID-19 infection affects a person's health or leads to the use of healthcare services), U09.9! (Post-COVID-19 condition, unspecified;), U10.9 (Multisystem inflammatory syndrome associated with COVID-19, unspecified), or G93.3 (Myalgische Enzephalomyelitis/Chronisches Fatigue-Syndrom (ME/CFS). The Studies at Charité – University Medicine Berlin, which represent a major reference for research on Long/Post-COVID and ME/CFS, have shown that post-COVID syndrome can persist for more than 20 months after infection and encompass the full spectrum of post-infectious ME/CFS [18, 19]. The main features are moderate to severe fatigue and exercise intolerance, which meet the Canadian consensus criteria for ME/CFS.

The inclusion of U08.9 was based on the WHO Definition [20] and on the German national S1 guideline “Long/Post-Covid” [3]. Data from published studies also confirm widespread use of U08.9 diagnosis: For instance, the study of Ollila et al., [21] showed the distribution of codes used in Post-Covid-Syndrom: U09.9! = 12.1% and U08.9 = 47.4%. The rationale for including U08.9 was a higher sensitivity in identifying patients with probable Long/Post-COVID manifestations. The ICD code G93.3 will be taken into account only for patients with a previous COVID-19 infection. For ICD codes U09.9!,U08.9 and U10.9, a single code entry is sufficient.

In addition, the analyses will be repeated for insured persons with an outpatient or inpatient COVID-19 diagnosis (ICD: U07.1) between 2020 and 2024 as a risk population (see the following section, “Sensitivity analyses”).

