## Study participants

**Table Taba:** 

*Aim 1:*	*Participants*
Estimation of incidence and time trends of Long/Post-COVID in people with diabetes compared to those without diabetes, and analysis of potential risk factors for Long/Post COVID	All SHI-insured people in Germany (2021: 73.32 million; 2023: 74.31 million) stratified by diabetes status in the years 2021 to 2024
*Aim 2:*	
Analysis of mortality, any hospitalization, and hospitalization due to acute myocardial infarction, stroke, amputation, and DFS within 12, 24, and 36 months after Long/Post-COVID diagnosis in people with diabetes compared to those without diabetes, and identification of potential risk factors for these conditions	All SHI-insured people with and without an initial diagnosis of Long/Post-COVID, stratified according to diabetes status, will be monitored for a maximum of 36 months with regard to mortality and hospitalization due to relevant morbidity The cohort of Long/Post-COVID cases in 2021 and 2022 will be observed for up to 36 months; The cohort of Long/Post-COVID cases in 2023 will be observed for up to 12 months

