### Statistical analysis

*Aim 1* The incidence rate of Long/Post-COVID will be estimated separately in the population with and without diabetes and compared as relative risks. The incidence rates will be analyzed standardized by age and sex, using the entire German population as standard population. As SHI data will be used, the person time will be calculated by summing all quarters of the insurance time of insured persons under risk. The relevant insurance time ends on the earliest of the following: the date of first diagnosis of Long/Post-COVID (index date), the end of insurance time (e.g. death) or the end of the observation period (i.e. December 31, 2023).

In addition, Poisson regression models will be used to examine the time trend of the incidence rate of Long/Post-COVID. Since only 3 years will be available, we will only compare the incidence rates of 2022 and 2023 with those of the year 2021 as reference category. Moreover, the impact of potential risk factors such as age, sex, comorbidities (CHD, COPD, asthma, obesity, depression) and region (urban vs. rural, Eastern vs. Western Germany) will be analyzed with these models. We will consider each comorbidity as well as region separately in order to explore their role independently. We will estimate incidence rates stratified by diabetes and these variables. We further plan to perform regression models adjusted for each variable and diabetes as well as models stratified by diabetes. Thus, we intend to explore whether obesity is a further confounder or effect modifier in our analysis, even in the light of probable underreporting in administrative data. To take into account over-dispersion of the outcome variable, all analyses were conducted with the de-scale adjustment [22].

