## Discussion

Our project will contribute to gaining new insights into open questions regarding the association between diabetes and Long/Post-COVID. The results of the study will provide reliable epidemiological data on the incidence, relative risk, and time trends for Long/Post-COVID in people with diabetes which might influence health research and health policy decisions. Results will be reported in accordance with the STROSA guidelines [23].

Several expected limitations should be considered. Misclassification cannot be excluded, as the validity of coding for Long/Post-COVID conditions may vary due to differences in awareness and documentation practices across healthcare settings. Furthermore, the lack of information about the severity of symptoms could influence the risk assessment. Residual confounding cannot be excluded, as factors such as vaccination status could not be taken into account. Moreover, our analyses will not be further stratified by diabetes type since this would cause statistical power problems due to the expected small sample size.

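### The Aim 1 relative risk is open to differential ascertainment by diabetes status, probably upward but of unknown size, and no planned analysis described in the article equalises contact frequency

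*Protocol article*

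**What the plan says.** All places are in the protocol article.

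- **Exposure** (Study design and data sources): diabetes status is "defined according to an established algorithm based on antihyperglycemic prescriptions and outpatient and inpatient diagnoses".
- **Population** (Study participants table, Aim 1): "All SHI-insured people in Germany (2021: 73.32 million; 2023: 74.31 million) stratified by diabetes status". No contact requirement is stated for either group.
- **Denominator** (Statistical analysis, Aim 1): "the person time will be calculated by summing all quarters of the insurance time of insured persons under risk".
- **Outcome** (Study design and data sources): "For ICD codes U09.9!,U08.9 and U10.9, a single code entry is sufficient". G93.3 counts only after a previous COVID-19 infection. U08.9 is glossed as follows: "this code is used if a previous confirmed COVID-19 infection affects a person's health or leads to the use of healthcare services".
- **Adjustment** (Statistical analysis, Aim 1): rates are standardised by age and sex. The Poisson models name age, sex, five comorbidities and region. No measure of care use is among them.
- **Sensitivity analyses** (end of Statistical analysis): one repeats the Aim 1 rates and relative risks only in people with an outpatient or inpatient COVID-19 diagnosis. Another widens the outcome to functional and somatoform disorders because of possible underreporting.
- **Limitations** (Discussion): "the validity of coding for Long/Post-COVID conditions may vary due to differences in awareness and documentation practices across healthcare settings". Residual confounding is also acknowledged. Capture that differs by diabetes status is not mentioned.

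**The concern.** Exposure and outcome are both read from care records. A person classed as having diabetes has recorded care by construction, while the reference group includes insured people with little or no contact. A would-be case who stays out of care adds reference person-time but no event. Among people who do attend, more frequent visits give more chances for a code, and one entry is enough. The wording of U08.9 makes use of care part of the outcome. The article cites a study in which U08.9 made up 47.4% of the codes used, against 12.1% for U09.9!, so this code could carry much of the case count.

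The Background asks whether diabetes per se raises the risk of Long/Post-COVID. A relative risk modestly above 1 could come from a difference in the opportunity to be coded. With about 73 million insured people it could also have a narrow confidence interval and look settled.

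**Working it through.** The article gives no expected relative risk, contact rate or coding rate, so there is no figure to reproduce. The check asks how much distortion the design permits. All inputs below are assumptions unless a section is named.

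**Model.** Let s1 and s0 be the probabilities that a true case is coded, with and without diabetes. Then apparent RR = true RR × s1/s0. The true RR is set to 1.00 throughout.

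**1. Upper bound for a given loss in the reference group.** Let p be the share of would-be reference cases never coded, so s0 = 1 − p. The ratio is largest when s1 = 1, giving 1/(1 − p):

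- p = 5%: 1/0.95 = 1.05
- p = 10%: 1/0.90 = 1.11
- p = 15%: 1/0.85 = 1.18
- p = 20%: 1/0.80 = 1.25

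**2. Symptoms bring some people into care.** Let q be the share of would-be reference cases among people without usual contact, and h the fraction of these who stay uncoded. Then p = q × h.

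- h = 0.5, q = 5%, 10%, 20%: 1/0.975 = 1.03; 1/0.95 = 1.05; 1/0.90 = 1.11
- h = 0.1, q = 5%, 20%: 1/0.995 = 1.005; 1/0.98 = 1.02

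**3. Attribution to diabetes.** The Background says that post-COVID condition needs symptoms not explained by something else. If a share a of cases with diabetes is put down to diabetes, s1 = 1 − a and the ratio is (1 − a)/(1 − p):

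- a = 5%, p = 10%: 0.95/0.90 = 1.06
- a = 10%, p = 10%: 0.90/0.90 = 1.00
- a = 10%, p = 5%: 0.90/0.95 = 0.95
- a = 20%, p = 10%: 0.80/0.90 = 0.89

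**4. Contact frequency among people who all have contact.** With v contacts and coding probability c per contact, s = 1 − (1 − c)^v.

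| c | 8 vs 6 contacts | 8 vs 4 contacts |
|---|---|---|
| 0.05 | 1.27 | 1.82 |
| 0.10 | 1.21 | 1.66 |
| 0.20 | 1.13 | 1.41 |
| 0.40 | 1.03 | 1.13 |

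Example: c = 0.20, 8 vs 6 contacts, (1 − 0.8^8)/(1 − 0.8^6) = 0.832/0.738 = 1.13. This part survives any restriction that only requires some contact. When c is low, the uncoded share is far above 20%, so the range in step 1 does not cap the total bias.

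**5. Scale.** The odds ratios for comorbidities quoted in the Background run from 1.19 to 1.38. Loss in the reference group alone would need p = 1 − 1/1.19 = 16% to produce the first and p = 1 − 1/1.38 = 28% to produce the second.

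**6. Precision.** With an assumed 10,000 cases with diabetes and 90,000 without, the standard error of log RR is √(1/10,000 + 1/90,000) = 0.0105. The 95% interval is about ±2% before over-dispersion scaling, so a distortion of 5% would exceed sampling error.

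**The case against.** A reader might infer three stronger claims, which the documents do not support.

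- **That the relative risk is biased upward.** The article gives no contact or coding rates, and attribution of symptoms to diabetes works the other way. Upward is the expected direction, not an established one.
- **That people without physician contact cannot become cases.** Symptoms can themselves bring a person into care, and one code at any time up to the end of 2023 suffices. Only would-be cases who stay out of care are lost.
- **That 1.05 to 1.25 is the expected bias.** It is the upper bound for an assumed p, where p is a share of would-be cases, not of person-time without contact.

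The plan also has partial safeguards. In the analysis limited to people with a recorded COVID-19 diagnosis, everyone has at least one documented contact, so never-contact people drop out of both groups. The planned rates by diabetes and comorbidity help too: within a stratum defined by a recorded comorbidity, both groups have recorded care. Neither equalises contact frequency, and the COVID-19 code itself depends on contact. The functional and somatoform expansion needs the same contacts, so it cannot reveal the problem.

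Finally, all insured people are the natural denominator for a population incidence of diagnosed disease, and an article may leave finer strata to a fuller document. The first argument stands, and the primary analysis should stay. The second has some force, since the list of model variables is given as examples. But the article sets out its sensitivity analyses and its limitations, and neither addresses capture that differs by diabetes status.

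**Conclusion.** The point holds as a design weakness that is cheap to address. The Aim 1 relative risk is open to differential ascertainment by diabetes status, probably upward, of unknown size, and only partly addressed by the planned analyses. Loss of reference cases alone gives at most 1.05 to 1.25 from a true 1.00 for an assumed p of 5% to 20%, and 1.03 to 1.11 if half of the would-be cases without usual contact (assumed 5% to 20%) still get coded. Differences in visit frequency could add to this, and attribution to diabetes could cancel or reverse it. The incidence of diagnosed Long/Post-COVID remains a valid description of what is coded. What is not secure is reading the relative risk as an effect of diabetes per se.

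**What to change.** 1. Keep the all-insured analysis as primary.
2. Add an Aim 1 sensitivity analysis that requires, in both groups, at least one outpatient contact in the four quarters before each at-risk quarter. Stratify it by the number of contact quarters (for example 1–2, 3, 4) or adjust for that number. The contact requirement alone would not deal with frequency.
3. Optionally, run the same diabetes contrast on one negative-control outcome fixed in advance: an acute diagnosis not plausibly related to diabetes or COVID-19.
4. State the reading rule beforehand. Treat the relative risk as a diabetes effect only if it persists in the contact-restricted and stratified analysis and, where a negative control is used, the relative risk for that outcome is close to 1. A raised negative-control value would point to ascertainment.
5. Name differential ascertainment by diabetes status in the limitations.

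The cost is extra runs on data of the kind already planned. The article already uses COVID-19 diagnoses from 2020, so a four-quarter look-back for 2021 appears feasible. The downside is that the restricted result applies to care users only, and contact frequency partly reflects morbidity, so conditioning on it may remove some real effect. For that reason it should stay a sensitivity analysis.

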*Aim 2* Age- and sex-standardized mortality and hospitalization rates will be estimated within 12, 24, and 36 months after a Long/Post-COVID diagnosis between 2021 and 2024. The data base will be a population-based cohort consisting of all insured persons with an inpatient or outpatient Long/Post-COVID diagnosis. All mortality and hospitalization rates will be calculated separately for insured people with and those without diabetes and will be compared using relative risks. In order to overcome potential confounding, Cox regression models will further be performed to investigate the impact of the aforementioned potential risk factors, as well as the year of Long/Post-COVID diagnosis. As we will conduct Cox models, we will only assess the time to first hospitalization with the date of hospital admission as index date. We will also consider death as competing risk in analyses with hospitalization as outcome.

Sensitivity analyses:Estimation of incidence rate of Long/Post-COVID in the population with and without diabetes and the corresponding relative risks as decribed in aim 1 using only insured persons with an outpatient or inpatient COVID-19 diagnosis as population at riskRepetition of analyses of aim 2 using only persons with an inpatient or outpatient Long/Post-COVID diagnosis and an additional previous COVID-19 diagnosis as population at riskExpansion of the outcome “Long/Post-COVID” to include comparable differential diagnoses (functional and somatoform disorders) in order to minimize the risk of bias resulting from potential underreporting of Long/Post-COVIDComparison of people with Long/Post-COVID and those with a differential diagnosis, stratified according to diabetes statusRepetition of main analyses of aim 1 and aim 2 with the modified outcome.

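### The rule that every Long/Post-COVID code is incident by definition fits the three U codes but not G93.3, nor the functional and somatoform disorders added in the expanded outcome

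*Protocol article*

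**What the plan says.** In the protocol article, Study design and data sources, the outcome is defined by four ICD codes: U08.9, U09.9!, U10.9 and G93.3 (ME/CFS). A Long/Post-COVID diagnosis is "considered as first or incident event per se (no counting of reinfections), as this diagnosis has only been established since 2021".

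Two further rules follow in the same section. For the U codes: "For ICD codes U09.9!,U08.9 and U10.9, a single code entry is sufficient". For the fourth code: "The ICD code G93.3 will be taken into account only for patients with a previous COVID-19 infection". The article states no look-back or event-free entry period for any outcome code.

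Under Statistical analysis, aim 1, person-time is closed by the first code: "The relevant insurance time ends on the earliest of the following: the date of first diagnosis of Long/Post-COVID (index date". The time trend takes the first observed year as its base: "we will only compare the incidence rates of 2022 and 2023 with those of the year 2021 as reference category".

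The sensitivity analyses widen the outcome "to include comparable differential diagnoses (functional and somatoform disorders) in order to minimize the risk of bias" from under-reporting. The main analyses of both aims are then repeated with this modified outcome. That clause mentions neither a previous COVID-19 diagnosis nor a look-back.

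**The concern.** Declaring the first observed code incident is safe only if the code could not have been used before observation began. The article's reason, that the diagnosis dates from 2021, gives that assurance for the three codes whose labels name COVID-19. G93.3 denotes a chronic condition that is not specific to COVID-19. The authors recognise this, because they admit it only after an infection. But that condition concerns the patient's infection history, not whether the ME/CFS code is new.

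A person with long-standing ME/CFS who is infected in 2022 and receives G93.3 again at a later visit therefore meets the definition. The Background section also requires, for the Post-COVID condition, that no other cause accounts for the symptoms. ME/CFS from before the infection is such a cause.

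Prevalent disease would then enter the incidence numerator. In aim 2, follow-up of 12, 24 and 36 months would start at a routine recoding rather than at onset. If the same reasoning is carried over to functional and somatoform disorders, which also existed before 2021, the prevalent share could be much larger. Most of it would surface in 2021, the reference year of the trend.

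**Working it through.** The article states no event count or power figure, so there is none to reproduce. The check reads the rules together and then illustrates size.

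**Does any stated rule remove prevalent G93.3?**
- The previous-infection condition keeps anyone who was infected and later recoded.
- The single-entry rule covers only the three U codes.
- The person-time rule ends at first diagnosis but states no event-free start.
- Restricting the population at risk to people with a COVID-19 diagnosis (aim 1), or requiring an additional previous COVID-19 diagnosis (aim 2), keeps exactly these patients.

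None removes it.

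**Inputs from the documents:** 73.32 million insured in 2021 (Study participants); almost 50% of the population registered as infected, and a frequency of 5–6% in adults, lower end used (both Background).

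**Assumed inputs:** prior prevalence of G93.3 of 0.05% to 0.5%; prior prevalence of functional and somatoform codes of 1% to 10%; ratio of prior prevalence with to without diabetes of 0.8 to 1.5; true relative risk of 1.0.

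**Main outcome.** True cases = 73.32 million × 0.5 × 0.05 = 1,833,000. Prevalent carriers who could be counted = 73.32 million × 0.5 × p. Observed RR = (0.05 + p × ratio) / (0.05 + p).

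| p | Carriers | Share of counted cases | Observed RR at ratio 0.8 / 1.5 |
|---|---|---|---|
| 0.05% | 18,330 | 18,330 / 1,851,330 = 1.0% | 0.998 / 1.005 |
| 0.1% | 36,660 | 36,660 / 1,869,660 = 2.0% | 0.996 / 1.010 |
| 0.5% | 183,300 | 183,300 / 2,016,300 = 9.1% | 0.982 / 1.045 |

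The carrier counts are upper bounds for each p, because they assume that every infected carrier is coded again and has no earlier U code. The infected fraction cancels from the share, but the 5% frequency does not. If fewer true cases are coded, the share rises. At 1.4%, the figure that the Background gives for children, true cases are 513,240 and the shares are 3.4%, 6.7% and 26.3%.

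**Expanded outcome, if no look-back is applied.** Carriers = 73.32 million × p, with no infection condition. Observed RR = (0.025 + p × ratio) / (0.025 + p), where 0.025 = 0.5 × 0.05.

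| p | Carriers | Share of counted cases | Observed RR at ratio 0.8 / 1.5 |
|---|---|---|---|
| 1% | 733,200 | 28.6% | 0.943 / 1.143 |
| 5% | 3,666,000 | 66.7% | 0.867 / 1.333 |
| 10% | 7,332,000 | 80.0% | 0.840 / 1.400 |

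**Trend in the expanded outcome.** Assume flat true incidence of 0.025 / 3 = 0.00833 a year, and that 80%, 15% and 5% of carriers are first seen in 2021, 2022 and 2023. The 2022 to 2021 ratio is (0.00833 + 0.15p) / (0.00833 + 0.80p): 0.60 at p = 1%, 0.33 at 5% and 0.26 at 10%. This is an apparent decline where there is none.

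**The case against.** The strongest reply is that the main outcome is barely touched. The previous-infection condition narrows the problem to carriers who were infected, were coded again and had no earlier U code. On the ranges above, the diabetes relative risk moves by a few percent at most. That stands. A reader might infer that the main diabetes comparison is invalid, or that a known and large number of false cases enters it. The documents do not support this. They give no prevalence for G93.3, the counts are upper bounds on an assumed value, and the infected share of almost 50% comes from registrations up to August 2025, while aim 1 ends on December 31, 2023.

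The second reply is that the expanded outcome is one condensed clause, and that a full protocol or analysis plan may define codes and a look-back. This stands in part. A reader might infer that any functional or somatoform code, old or new, will be counted, or that the expanded analysis would mainly measure how often such disorders are coded. The text speaks of comparable diagnoses and lists none, it does not restate the incidence rule there, and the prevalent share exceeds half only over part of the assumed range. What remains is that the only reason given for skipping a look-back cannot apply to these diagnoses, and the main analyses are to be repeated with them.

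Third, the article plans to compare people with Long/Post-COVID and people with a differential diagnosis by diabetes status. That displays the two groups separately but removes no prevalent cases.

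Silence in a condensed article does not excuse the G93.3 problem. There the rule and its reason are both written down, and the reason does not cover the code.

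**Conclusion.** The concern holds as a should-fix. The incident-by-definition rule is justified for U08.9, U09.9! and U10.9 only. Applied as written, it counts pre-existing ME/CFS recoded after infection as new disease, and no planned analysis corrects this.

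For the main outcome, the likely effect on the diabetes relative risk is small: 0.98 to 1.05 for a true 1.0, given G93.3 prevalence of 0.05% to 0.5%, a 5% frequency and prevalence ratios of 0.8 to 1.5. Absolute incidence (about 1% to 9% of counted cases on the same assumptions) and aim 2 index dates are more exposed.

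For the expanded outcome, the incidence, the relative risk (0.84 to 1.40 for a true 1.0) and the trend against 2021 could all be badly distorted if no look-back is applied. That is conditional on assumed prevalences and concerns a sensitivity analysis.

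**What to change.** 1. Limit the incident-by-definition rule, and its reason, to U08.9, U09.9! and U10.9.
2. Count G93.3 only if no G93.3 code appears in the available quarters before the first COVID-19 diagnosis and the first G93.3 code follows that diagnosis.
3. For each added functional or somatoform diagnosis, count only a first code after a stated code-free look-back, for example 4 quarters, as far as the data reach.
4. Do not require U07.1 in the whole-population version of the expanded outcome. That would change its population, drop infected people who have no code and work against its purpose of offsetting under-reporting. A version restricted to people with a COVID-19 diagnosis is already planned for aim 1.

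The cost is a change of wording, one extra look-back query, and the exclusion of people with too little prior insurance time. Four quarters before an infection in 2020 would need 2019 data. The article does not say whether these are available, so the look-back actually achieved should be reported.
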